**Fig. 2 Fig2:**
[figure not shown]
Treatment Steps

### Level 1: digital treatment - “Managing Insomnia"

Managing Insomnia is an evidence-based insomnia intervention, free by clinician prescription, developed by “This Way Up” - a digital therapies service through St Vincent’s Hospital, Sydney, Australia [17]. This therapy consists of 4 sessions, which the client guides themselves through at their own pace. Each session takes about one hour to complete and is designed to be completed at one session per week. Participants have up to 90 days to complete the program once they start. The sessions are presented in a comic-book like format, and patients are prompted to complete questionnaires and sleep diaries throughout the sessions to facilitate engagement with the material. The referring Psychologist is able to track the progress of the patient, including their commencement of the program and completion of each session, as well as their outcome measures collected at each session (Insomnia Severity Index and K-10 score). A brief check-in phone call 2 weeks after treatment prescription will be undertaken to check progress and support engagement with the program as needed. No therapeutic content will be delivered during the phone call [31]. If the patient is engaging well with the intervention, a subsequent phone call will be scheduled for another six weeks to coincide with treatment conclusion and to collect outcome measures. If the patient has not commenced the intervention at the initial 2 week check-in, or if the patient reports barriers to engagement, a second check-in phone call will be scheduled 2 weeks later. If the patient has not engaged with the digital therapy within 4 weeks of being prescribed the intervention, reasons for this will be discussed and options for discharge, on-referral and/or entry to another intervention level will be provided.

### Level 2: group program

The manualised CBTi intervention and sleep manual delivered during group intervention was refined by our Sleep Psychology team from an evidence-based insomnia treatment developed at Flinders University, Adelaide, Australia [32]. The intervention is 4 sessions and covers the key components of insomnia treatment – psychoeducation, sleep restriction therapy, stimulus control, cognitive therapy and relaxation training. Each session is 90 min, and there are a maximum of 6 participants in each group session. The experienced Psychologist and Intern Psychologist monitor participation and clinical outcomes during the group program.

### Level 3: 1:1 with sleep psychology intern

Patients assigned to this level will undergo treatment 1:1 with the Psychology Intern under supervision from the experienced Psychologist. Psychology interns/trainees have completed undergraduate psychology training and are post-graduate (Masters, Doctorate or PhD) students on clinical placement. The CBTi intervention described above for Level 2 may be provided along with additional evidence-based strategies as required depending on sleep or mental health comorbidities; such as cognitive behavioural therapy (CBT) for depression/anxiety, dream rescripting for nightmares, and Motivational Interviewing for CPAP adherence [33] for those with comorbid OSA. Each of these sessions are 60 min in duration and delivered at a weekly to fortnightly interval. The number of sessions depends on how many sessions the patient requires to achieve adequate symptom relief based on ongoing assessment and monitoring. Participation and clinical outcomes are monitored throughout.

### Level 4: 1:1 with experienced Psychologist

Patients assigned to this level will undergo treatment 1:1 with the experienced Psychologist. The experienced Psychologist will monitor participation and clinical outcomes during the 1:1 intervention program, and provide additional evidence -based strategies depending on sleep or mental health comorbidities (as described in Level 3 above). Discharge or on-referral will be provided at the conclusion of the treatment.

For Levels 2 to 4 - sessions will be delivered flexibly either face-to-face or via telehealth.

### Measures

Primary and secondary outcomes will be collected at two endpoints; pre- and post- service change, comparing the pre-implementation period as a pre-measure (old model of care) to those participating in the (NEW) model of care as the post-measure.

#### Primary outcomes

##### Service access measures

Access measures include new patient activity for the sleep psychology service, and time from referral to treatment commencement and discharge within the sleep psychology service when comparing patients treated under the old model of care compared to those treated under the new model of care. Number of clinical occasions of service will be collected for the sleep psychology service and the medical service and compared for those attending under the old model of care compared to those attending under the new model of care. 

##### Patient-related outcomes

Patient-related primary outcomes will test non-inferiority in change scores on key clinical outcome measures from pre- to post- intervention when comparing those patients treated under the old model care compared to those treated under the new model of care. Furthermore, % patients treated adequately at each step of the Stepped Care Model will be measured by the number of patients discharged from the service by the treating clinician with outcome measures indicating reliable clinical change from pre- to post- intervention. The Clinical outcome measures include the Insomnia Severity Index (ISI) [34], Depression Anxiety and Stress Scale (DASS-21) [35], Kessler Psychological Distress Scale (K10) [36], and the EuroQol (EQ-5D-5 L) [37].

**Insomnia Severity Index** (ISI) is a 7-item self-report questionnaire assessing the nature, severity, and impact of insomnia over the past two weeks on a 5-point scale from 0 = no problem; 4 = very severe problem. The measure is widely used in the literature as well as clinically where a score of 11 is indicative of likely meeting criteria for an insomnia disorder in clinical trials and a change score greater than 8 is the minimally important difference to be considered ‘markedly improved’ or in remission [34, 38].

**Depression Anxiety and Stress Scale** (DASS-21) is a short version of a 42-item self-report instrument designed to measure three related negative emotional states: depression, anxiety and tension/stress over the past 7 days. Items are scored on a 3-point scale from 0 (did not apply to me at all) to 3 (applied to me very much, or most of the time). Total scores represent symptoms of distress in each of the domains in the ‘normal’, ‘mild’, ‘moderate’, ‘severe’ and ‘extremely severe’ relative to population norms [35].

**Kessler Psychological Distress Scale** (K10): The K10 is a 10-item self-report scale to assess symptoms over the past 4 weeks. Items are rated on a 5-point scale from 1 (none of the time) to 5 (all of the time). A score of less than 20 represents low psychological distress ‘likely to be mentally well’. Between 20 and 24 represents moderate distress ‘may have a mild mental disorder’ and between 25 and 29 represents high psychological distress ‘likely to have a moderate mental disorder’ [36].

**EuroQol** (EQ-5D-5 L): The EQ-5D-5 L measures five dimensions of quality of life: mobility, self-care, usual activities, pain/discomfort and anxiety/depression. Each dimension has 5 levels: no problems, slight problems, moderate problems, severe problems, and extreme problems. The EQ VAS records the patient’s self-rated health on a vertical visual analogue scale where the endpoints are labelled ‘The best health you can image (100)’ and ‘The worst health you can image (0)’. The EuroQol also allows preliminary health economics evaluation by performing quality-adjusted life year calculations as a measure of cost-effectiveness of the intervention compared to standard care [37].

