#### Direct to psychology stepped care

All patients referred to sleep psychology will complete an initial assessment according to Diagnostic and Statistical Manual (DSM-V-tr) and International Classification of Diseases (ICD-11) criteria [26, 27], including outcome measures (see *Measures).* For patients referred ‘Direct to Psychology’ additional measures will manage any potential risks associated with psychology as first contact within the model due to potential ‘missed’ medical clinical indications. These measures will include screening tools for Obstructive Sleep Apnoea (OSA) (using items from the STOP-BANG [28] and Berlin Apnoea [29] Questionnaires), hypersomnolence disorders (using items from the Cataplexy Questionnaire [30] and questions related to the presence of neuromuscular conditions, respiratory conditions and driving risk.

The inclusion criteria for Direct to Psychology criteria as defined in stakeholder co-design activities [24] include;

(i)being referred for insomnia and/or sleep psychology, and/or(ii)suboptimal adherence to OSA treatment including continuous positive airway pressure therapy (CPAP) or mandibular enhancement splint (MAS) if medical management has been already optimised.

Exclusion criteria include;

(i)significant new/changed sleep disordered breathing (or identified significant sleep disordered breathing)(ii)highly comorbid patients (e.g., neuromuscular conditions/weakness, respiratory conditions), diagnosis of hypersomnia/question of central disorder of hypersomnolence(iii)category 1 (urgent) referrals(iv)driving risk.

Patients identified as meeting the inclusion and exclusion criteria will proceed with Psychology-first intervention as indicated. Patients who meet the exclusion will be redirected back to the Standard Care model and may be re-triaged by the attending medical officer based on the additional information gleaned from the psychological assessment.

Patients progressing to psychological treatment will be matched to the appropriate treatment level. Depending on patient engagement and participation with the treatment level, as well as clinical outcomes on key assessment measures; discharge, on-referral and/or entry to another intervention level will be provided. The proposed steps of care in the new model are outlined in Fig. 2.

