*How effective was the model of care in achieving its intended outcomes?*	**Effectiveness** – impact on outcomes and quality of life/economic outcomes	**Primary outcomes** *Service Access Measures* • Average number of occasions of Service within Sleep Psychology service under ‘old’ model compared to ‘new’ model of care • Percentage of new patient activity under ‘old’ model compared to ‘new’ model of care • Average wait-time to access a first appointment with Sleep Psychology from date of referral under ‘old’ model compared to ‘new’ model of care • Average time to discharge from first appointment to final appointment with Sleep Psychology under ‘old’ model compared to ‘new’ model of care • Percentage of patients discharged from psychology *Patient-related Outcomes* • Change scores on clinical outcome measures pre- to post- treatment on clinical outcome measures (ISI, DASS-21, K10 and EQ-5D-5 L) comparing patients treated under ‘old’ model versus ‘new’ model of care • % patients treated adequately at each level of Stepped Care • Differences in patient characteristics (age, sex, geographical location, presenting issue) between those who are adequately treated at each level of the new model of care (moderation analysis) *Economic Outcomes* • Quality-adjusted life year calculations as a measure of cost-effectiveness of the ‘new’ model of care compared to the ‘old’ model of standard care **Secondary outcomes** *Patient satisfaction* • Patient satisfaction measure (SRS) post- treatment comparing patients treated under ‘old’ model versus ‘new’ model of care *Patient satisfaction with digital intervention* • Patient reported ease of access to digital intervention • Acceptability and relatability of the online program/service provided (rated by patients), including: i. motivation to access online treatment (diversion from public hospital services for insomnia treatment) ii. understanding of intervention materials iv. perceived change in sleep problem • Differences in patient characteristics (age, sex, geographical location, presenting issue) between those who complete the digital intervention compared to those who do not complete	Significantly fewer occasions of service under new model of care Significantly greater % new patient appointments under new model Significantly shorter wait-time to first appointment under new model Significantly shorter time to discharge under new model Outcomes are non-inferior under new model of care; upper bound 95%CI on outcome measures is less than MCID MCID is achieved on outcome measures by > 80% patients at each level The ‘new’ model is more cost effective Patient reported satisfaction is non-inferior under new model of care; upper bound 95%CI is less than MCID > 90% patients report positive experiences	Patient qualitative and quantitative surveys Medical Record Patient registration system

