### Statistical analysis

The project will employ a mixed methods approach. Qualitative surveys for patients, multidisciplinary staff, and referrers was undertaken pre-service change to ascertain the acceptability of the digital therapy, as well as familiarity, access, confidence, and relatability of this treatment option [25]. Post-implementation surveys will also be undertaken on these same metrics. Quantitative data will be collected pre- and post-service change to ascertain treatment effectiveness in terms of clinical outcome measures, as well as service measures of interest such as patient flow, occasions of service and program engagement. Based on similar studies [40], and allowing for some incomplete data, we expect to have data for approximately 110 participants from each pre- and post- time period, resulting in a sample of 220 participants overall who will be suitable for the Direct to Psychology pathway. To assess wait times, participants will be categorised into four groups based on the time-period (pre/post implementation) and whether they met eligibility criteria for the Direct to Psychology pathway. Differences in wait times between the groups will be assessed using a one-way Analysis of Variance (ANOVA) and linear regression modelling. In a one-way ANOVA study, a sample of 220 participants, divided by 4 groups, achieves 80% power with a significance level of 0.05 to detect a moderate-large effect size (Cohen’s f) of 0.25 [41]. The effects of other variables of interest and potential confounders (patient characteristics, diagnosis,) will be tested in multivariable models. For differences in patient outcome measures pre- and post- intervention when comparing pre- and post- service change, the mean between-group difference and 95% confidence interval (CI) will be calculated. As this aspect of the evaluation is a non-inferiority trial (that is, we expect clinical outcomes to not be reduced due to the service change), the criteria adopted to determine non-inferiority will be if the upper bound 95%CI on each clinical outcome measure was less than the minimal clinical important difference (MCID). Quantitative data measuring pre- and post- service change outcomes on key indices of patient service satisfaction, service characteristics (e.g., occasions of service); as well as referrer and staff service satisfaction, and engagement with digital therapies, will be evaluated via univariate statistical tests where indicated such as independent samples t-test (or nonparametric equivalent), and categorical comparisons will be evaluated using Pearson’s chi-square. The distribution of outcome measures will be assessed, and appropriate transformations will be applied for use in modelling. Differences between group means will be tested using generalised linear regression modelling. Health related quality of life will be measured pre- and post- implementation using the EQ-5D-5 L. Population norms for EQ-5D-5 L Australia will be used to value the data set [42].

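### The ISI non-inferiority margin for group means is the full MCID, a change above 8 points that marks an individual patient as much better or remitted, and is too lenient for that use

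*Protocol article*

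**What the plan says.** Under Patient-related outcomes, the article makes this a primary comparison: "Patient-related primary outcomes will test non-inferiority in change scores on key clinical outcome measures". The Statistical analysis section names the estimate, "the mean between-group difference and 95% confidence interval (CI) will be calculated", and then the decision rule: non-inferiority is accepted "if the upper bound 95%CI on each clinical outcome measure was less than the minimal clinical important difference (MCID"). The RE-AIM table repeats the rule as its target: "Outcomes are non-inferior under new model of care; upper bound 95%CI on outcome measures is less than MCID". Neither place takes a fraction of the MCID or says how much of the old model's benefit must be preserved.

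The only MCID with a number is the one for the ISI, under Patient-related outcomes: "a change score greater than 8 is the minimally important difference to be considered" markedly better or remitted. The ISI has seven items, each rated "on a 5-point scale from 0 = no problem; 4 = very severe problem", so its total runs from 0 to 28. The RE-AIM table also uses the MCID at patient level, as a change that more than 80% of patients at each treatment level should reach.

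**The concern.** A change that marks one patient as a clear success answers a different question from the loss in average change that a service can accept. The first is a large individual improvement. The second should be small against the average benefit of the old model, or a finding of non-inferiority says little about whether that benefit was kept. The article moves the first into the place of the second without giving a reason.

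Equivalent clinical outcomes are one of the stated hypotheses. They are the safeguard on a redesign whose other aims are shorter waits and lower cost, and the Discussion looks ahead to using the model in other services. A lenient margin weakens that safeguard.

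**Working it through.** **Inputs from the article.** ISI margin 8 (Patient-related outcomes, applied through the Statistical analysis rule); about 110 patients per period (Statistical analysis); two-sided 95% confidence interval.

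**Assumed, because the article does not give them.** SD of ISI change 4 to 8. The mean ISI benefit under the old model is left open and treated as an unknown. I also assume that the 110 per period all contribute ISI change scores, and show 55 per period as a less favourable case.

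**The plan's own figure.** No power or sample size is stated for the non-inferiority comparison. The only power figure, 80% for the wait-time ANOVA (220 patients, four groups, f = 0.25), recomputes to 88.4%. It concerns another outcome and has no bearing here.

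**Step 1: the largest observed deficit that passes.** Half-width = t(0.975, 2n − 2) × SD × √(2/n); largest passing deficit = 8 − half-width. At SD 6 and n = 110, SE = 6 × √(2/110) = 0.809, half-width = 1.59, and 8 − 1.59 = 6.41.

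| SD | half-width | largest passing deficit | old-model benefit of which this is half |
|---|---|---|---|
| 4 | 1.06 | 6.94 | 13.9 |
| 5 | 1.33 | 6.67 | 13.3 |
| 6 | 1.59 | 6.41 | 12.8 |
| 7 | 1.86 | 6.14 | 12.3 |
| 8 | 2.13 | 5.87 | 11.7 |

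The last column is twice the third, before rounding. If the old model's mean benefit is below that value, a deficit of more than half of it can pass. At SD 6 the largest passing deficit is 80% of a benefit of 8 points, 64% of 10, 53% of 12 and 46% of 14.

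**Step 2: the chance of passing for a given true loss d.** P = Φ((8 − d)/SE − 1.96), with n = 110.

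- d = 5, SD 6: Φ(3/0.809 − 1.96) = 0.96. Across SD 5 to 8 it runs from 0.99 to 0.79.
- d = 6, SD 6: 0.70.
- d = 7, SD 6: 0.24.
- d = 8: 0.025.

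**Step 3: what a pass can look like.** At SD 6, an observed deficit of 5 points has the interval 5 ± 1.59, or 3.41 to 6.59. It excludes zero, so the new model is significantly worse. It also lies below 8, so the new model is non-inferior by the rule.

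**Step 4: the same design with a 4-point margin.** Power at no true difference = Φ(4/SE − 1.96).

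- n = 110: above 99.9% at SD 5, 99.9% at SD 6, 98.9% at SD 7, 96% at SD 8.
- n = 55: 93.8% at SD 6, 85% at SD 7, 74.6% at SD 8.

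For 80% power, a margin of 8 needs only 7 to 16 patients per period (SD 5 to 8) and a margin of 4 needs 25 to 63.

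**The case against.** A reader might infer that the new model could lose most of the treatment benefit and still pass. The article does not establish this, because it gives no mean change under the old model. Its one related figure is the target that more than 80% of patients reach the MCID. That target is set for the new model, but if old-model changes were normal with 80% above 8, their mean would be 8 + 0.84 × SD, or about 13.05 at SD 6. The largest passing deficit would then be 6.41/13.05 = 49% of the benefit (61% at SD 4, 40% at SD 8). The objection stands: how much of the benefit could be lost depends on a number the article does not state.

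A reader might also infer that passing is nearly automatic. It is not. At SD 6 the chance of passing falls to 70% at a true loss of 6 points and 24% at 7. The rule is lenient towards moderate losses and rejects large ones.

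The plan also reports the mean difference with its interval and tests group means by regression. A true 5-point deficit would be statistically significant more than 99% of the time (SD 6 to 8, 110 per period). The loss would therefore be visible, but the stated rule would still label it non-inferior, and that label decides the hypothesis.

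Patients can also enter for "suboptimal adherence to OSA treatment including continuous positive airway pressure therapy (CPAP") or splint therapy. Some of them may have little insomnia, which would pull an ISI difference towards zero. The two entry criteria are joined by and/or, however, and no share without insomnia is given, so the size of any dilution cannot be stated.

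Lastly, numeric margins for the other instruments may stand in the full protocol or analysis plan. Their absence from an article is not a fault.

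**Conclusion.** The point holds as a badly fixed decision threshold on a primary outcome. The article states the rule twice, and the only value it offers for that rule is an individual-success threshold equal to 8/28 = 29% of the ISI range. With 110 per period, observed mean deficits of up to 6.9 to 5.9 points pass (SD 4 to 8). At SD 6, a true 5-point loss is called non-inferior about 96% of the time (79% to 99% for SD 8 to 5).

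The largest passing deficit exceeds half of the old-model benefit if that benefit averages below about 12 points (11.7 at SD 8, 13.9 at SD 4). For larger mean benefits it does not. These figures rest on the assumed SD and on 110 analysable patients per period. That the threshold is an individual one does not depend on either.

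**What to change.** Before the two periods are compared, replace the ISI criterion with a fixed numeric margin for the between-group difference in mean change. It should be clearly smaller than 8 and come with a written reason that refers to the benefit expected under the old model. No more than half the stated MCID, 4 points, is an example of a ceiling; the article does not itself imply that value. Keep an ISI change above 8 only as the definition of individual response. Apply the same principle to the other instruments, so that no threshold for individual change serves as a group-mean margin.

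An ISI analysis limited to patients with a baseline score of at least 11, the article's own cut-off, could be added as support. It should not replace the main comparison, because it narrows a deliberately broad population and reduces the sample by an unknown amount.

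The cost is a change of wording and a stricter criterion. At 110 per period, a 4-point margin needs no extra patients for SD 5 to 8 (power 96% or more at no true difference). If only 55 per period have usable scores, power is about 94% at SD 6 but 75% at SD 8, so the number with complete ISI data should be checked when the margin is set.
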